**2. Sample Size Estimation**

Assuming the endpoint FMA-LE scale value in the preconditioned iTBS group is 3 points higher than in the non-preconditioned iTBS group, and the combined standard deviation for all groups is 2.5 points. Based on existing research results and clinical experience, at a statistical significance level of α=0.05, to achieve 90% statistical power, and considering a 20% follow-up loss rate, calculation using PASS 15 software indicates: at least 20 patients are needed per group, totaling 60 patients.

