**3. Random Grouping**

A total of 60 eligible stroke patients will be enrolled in this study. Following the baseline assessment, a computer-generated randomization sequence will be used to assign all participants in a 1:1:1 ratio to one of three parallel intervention groups: the priming iTBS group (n=20), the non-priming iTBS group (n=20), or the sham stimulation group (n=20). The allocation sequence will be concealed from the researchers enrolling participants. After a participant provides informed consent and all baseline assessments (T0) are completed, the research coordinator will access the central web-based system. The system will then reveal the group allocation only to the unblinded physical therapist responsible for administering the intervention. This ensures that outcome assessors and participants remain blinded.

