**6. Statistical Analysis**

SPSS 22.0 software will be used. Demographic and baseline characteristics will be compared using one-way analysis of variance (ANOVA) or Fisher's exact test. Mixed-design ANOVA (between-subjects factor: group; within-subjects factor: time) and the interaction between time and group will be analyzed to compare dependent outcomes across groups at the three time points (T0-T0, T1-T0, and T2-T0). The significance level is set at P < 0.05. If any significant time-by-group interaction effects are found, pairwise t-tests will be used for comparisons, comparing baseline changes with a Bonferroni correction threshold of 0.017. If any significant time-by-group interaction effects are found, exploratory subgroup analyses will be conducted to investigate potential differential effects among different functional groups. Due to the exploratory nature of the study, we applied the Bonferroni correction only in the post-hoc comparisons of the primary outcome (P=0.017, number of comparisons=3).

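### Group comparisons on change from baseline ignore baseline FMA-LE as a covariate; they are valid but less precise than a baseline-adjusted analysis

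*Protocol*

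**What the plan says.** Protocol Section 6 sets out two steps. The first is a mixed-design ANOVA with group and time as factors, applied to differences from T0 up to T2. If the time-by-group interaction is significant, the second step follows: "pairwise t-tests will be used for comparisons, comparing baseline changes with a Bonferroni correction threshold of 0.017". The 0.017 threshold covers three comparisons and applies to the primary outcome, FMA-LE. Neither step includes a baseline covariate.

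Section 2 sizes the trial on a between-group difference at the endpoint: "Assuming the endpoint FMA-LE scale value in the preconditioned iTBS group is 3 points higher than in the non-preconditioned iTBS group". It adds that "the combined standard deviation for all groups is 2.5 points". The other inputs are "at a statistical significance level of α=0.05", "to achieve 90% statistical power" and "considering a 20% follow-up loss rate", and the result is that "at least 20 patients are needed per group, totaling 60 patients". Section 2 does not say whether the SD belongs to the endpoint value, the change or an adjusted residual. No baseline-endpoint correlation is given anywhere.

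**The concern.** A change score does use the baseline, but with its coefficient fixed at 1. ANCOVA estimates the coefficient from the data. When the SDs at baseline and endpoint are equal, the best coefficient is ρ. Fixing it at 1 adds noise, and more of it the lower ρ is. The interaction test has the same feature, because it too compares changes between groups.

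In a trial that expects about 16 evaluable patients per arm, that noise can be expensive. At stake is the power of the contrast for which the trial was sized, primed against non-primed iTBS. The covariate that would recover the loss is already collected at T0.

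**Working it through.** **Inputs from the protocol.** Difference 3 points, SD 2.5, α=0.05, power 90%, loss 20% (Section 2); three arms at 1:1:1 (Section 3); pairwise threshold 0.017 (Section 6).

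**Assumptions, not in the protocol.** SD 2.5 at both T0 and endpoint; two-sided tests; ρ from 0.3 to 0.8, shown as a range.

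**Step 1: reproduce the stated size.** A two-sample t-test (noncentral t) with difference 3, SD 2.5 and two-sided α=0.05 needs 16 evaluable per arm for 90% power (power at 16 is 90.7%). Then 16/(1−0.20) = 20 per arm, which is the protocol's figure.

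**Step 2: SDs under the two analyses.**
- Change score: SD = 2.5×√(2(1−ρ))
- ANCOVA residual: SD = 2.5×√(1−ρ²)
- Variance ratio, ANCOVA to change: (1−ρ²)/(2(1−ρ)) = (1+ρ)/2

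**Step 3: small-sample cost of the slope.** For two arms of 16, the variance is inflated on average by 1 + 1/(32−4) = 1.036, and one degree of freedom is lost (29 instead of 30). ANCOVA stops gaining when 1.036×(1+ρ)/2 = 1, that is, at ρ of about 0.93.

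**Step 4: results for 16 evaluable per arm and a 3-point difference.** The ANCOVA power columns include the cost from step 3; the SD and variance-ratio columns do not.

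| ρ | SD change | SD ANCOVA | Variance ratio | Power at 0.017: change | Power at 0.017: ANCOVA | Power at 0.05: change | Power at 0.05: ANCOVA |
|---|---|---|---|---|---|---|---|
| 0.3 | 2.96 | 2.38 | 0.65 | 63.5% | 82.5% | 79.3% | 92.2% |
| 0.5 | 2.50 | 2.17 | 0.75 | 80.1% | 89.8% | 90.7% | 96.1% |
| 0.7 | 1.94 | 1.79 | 0.85 | 96.3% | 98.0% | 98.9% | 99.5% |
| 0.8 | 1.58 | 1.50 | 0.90 | 99.7% | 99.8% | 99.9% | >99.9% |

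**Step 5: separate the two effects.** At ρ=0.5 the change-score SD is exactly 2.5, so at α=0.05 the planned test has the 90.7% of step 1. Its fall to 80.1% comes entirely from moving to 0.017. What baseline adjustment contributes is the difference between the change and ANCOVA columns at the same α: at 0.017, about 19 points of power at ρ=0.3, 10 at 0.5, 2 at 0.7, and almost nothing at 0.8.

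**Step 6: chance imbalance.** The standard error of a baseline difference between two arms of 16 is 2.5×√(2/16) = 0.88 points. An imbalance of one standard error moves the change-score estimate by (1−ρ)×0.88, which is 0.62, 0.44 and 0.27 points at ρ = 0.3, 0.5 and 0.7, against a target of 3.

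**The case against.** The strongest reply is that nothing here is an error. A t-test on change is unbiased in a randomised trial, and it already makes some use of baseline. That stands. The shift in step 6 is conditional on an observed imbalance and averages to zero over randomisation, so a reader who infers that the planned comparison is biased goes too far.

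A reader might also infer that the analysis contradicts the sample size and leaves the trial underpowered, because Section 2 speaks of an endpoint value and Section 6 of changes. The protocol does not support that. Section 2 does not label the SD. If 2.5 is an SD of change, there is no mismatch of scale. If it is an SD of the endpoint value, the change score is noisier than planned below ρ=0.5 and less noisy above it, and the protocol does not say where ρ lies.

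It is equally tempting to blame change scores for the whole gap between 80% and 90% at ρ=0.5. Step 5 shows that this gap comes from sizing at 0.05 and testing at 0.017, which is a separate matter.

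Finally, the practical gain is small if ρ is 0.7 or more. That also stands, and it limits how strongly the point can be pressed. It does not remove the point: Section 6 names the less precise method outright, and up to ρ of about 0.93 adjustment does better.

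**Conclusion.** The point holds as a low-cost improvement in precision. On average the planned change-score comparisons are less precise than a baseline-adjusted analysis unless ρ exceeds about 0.93. The variance reduction is 35%, 25%, 15% and 10% at ρ = 0.3, 0.5, 0.7 and 0.8, before the cost of about 4% for the slope. In power at 0.017 the gain is large at ρ=0.3, useful at 0.5 and minor from 0.7 upwards.

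The power figures rest on an SD of 2.5 at both times, 16 evaluable per arm and a 3-point effect; the variance ratio needs only equal SDs. Since ρ is not stated, only the range can be defended. The algebra is firm, but the practical size of the gain in this trial is unknown.

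**What to change.** In Section 6, analyse post-baseline FMA-LE with baseline FMA-LE as a covariate. Either of two models will do: ANCOVA at T2, or a repeated-measures mixed model of the post-baseline visits with baseline as covariate and the visit for the group contrasts named in advance. Use the same model for the overall group test and for the three pairwise contrasts at 0.017. Replacing only the t-tests would leave the unadjusted interaction test deciding whether they are run. Report adjusted mean differences with 95% confidence intervals, and treat PASS and MBI in the same way.

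In Section 2, state whether 2.5 is the SD of the endpoint value, the change or the adjusted residual, give the assumed ρ where it is needed, and check the size against the chosen analysis. ANCOVA alone does not align the two sections.

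The cost is a short rewrite of Section 6 and a clarification in Section 2, with no new data. Statistically it is one degree of freedom, and a negligible loss if ρ exceeds about 0.93. Choosing ANCOVA at T2 also means naming T2 as the primary time point, which Section 5.1 does not do at present.

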**7. Safety Monitoring and Adverse Event Handling**

**7.1 Safety Monitoring**

**7.1.1 Monitoring Entities and Responsibilities**

- Safety Supervisor: Must hold a valid clinical physician license and have ≥3 years of clinical experience, responsible for monitoring the safety of the intervention process, focusing on risks related to TMS and robot-assisted training, and leading adverse event management.
- Physical Therapist: When performing TMS interventions and robot-assisted training, assess the patient's mental state, fatigue, pain, blood pressure, heart rate, and muscle tone in the affected limb before intervention using scales such as Borg CR10, VAS, Modified Ashworth Scale (MAS); during intervention, inquire about the patient's feelings every 10 minutes, monitor heart rate and respiration, have a blood pressure monitor and pulse oximeter ready; after intervention, record patient reactions.
- Rehabilitation Assessor: Assessments using fNIRS, three-dimensional gait analysis, EEG, sEMG, and MEP were conducted at three time points: baseline (T0), 2-week mid-intervention (T1), and immediately post-intervention at 4 weeks (T2). The FMA-LE and MBI were administered at T0, T1, T2, and at the 6-week follow-up (T3). Safety was evaluated by monitoring changes in all collected data, with any anomalies promptly reported to the safety monitor.

**7.1.2 Monitoring Content and Frequency**

- Vital Signs: Monitor heart rate and respiration every 10 minutes during robot-assisted training; measure blood pressure and heart rate before TMS intervention, monitor appropriately during intervention.
- Symptoms and Signs: Check patients for adverse symptoms such as hearing problems, local pain, and changes in limb function before and after each intervention; comprehensive assessment by the rehabilitation assessor at each assessment time point.
- Equipment: Check the TMS equipment cooling system, navigation calibration, and parameter settings before use; check robot battery, joint range of motion, and emergency stop function; pay attention to equipment operation during use, stop immediately if abnormal; record maintenance status after use; TMS equipment calibrated by the manufacturer every 6 months, robot calibrated annually.

**7.2 Adverse Event Handling**

**7.2.1 Definition of Adverse Events**

Refers to any unintended physical or psychological discomfort experienced by the patient during the study, regardless of its relationship to the intervention, including but not limited to hearing problems, local pain, muscle twitching, joint soreness, muscle fatigue, dizziness, seizures.

**7.2.2 Handling Procedures for Different Types of Adverse Events**

- Seizure: Immediately stop the intervention, lay the patient flat, turn head to one side to keep the airway clear, prevent injury; call for emergency help, monitor vital signs and record the seizure situation; if convulsions last more than 5 minutes or occur consecutively, administer antiepileptic drugs (e.g., diazepam) according to emergency guidelines; assist with further examination after condition stabilizes; report to the Ethics Committee and other relevant departments within 24 hours.
- Hearing Problems: Stop TMS intervention, let the patient rest in a quiet environment; check device sound output, refer to ENT if symptoms do not alleviate.
- Local Pain, Muscle Twitching, Joint Soreness, Muscle Fatigue: Reduce intervention intensity or suspend intervention, let the patient rest, apply cold/heat therapy as appropriate; adjust subsequent intervention parameters based on patient tolerance.
- Dizziness: Stop intervention, assist the patient to lie flat or sit quietly; measure blood pressure and heart rate, arrange further examination if symptoms do not alleviate or worsen.

**7.2.3 Adverse Event Recording and Reporting**

- Recording: After each intervention, promptly record the time of adverse event occurrence, manifestations, related intervention circumstances, handling measures, and outcomes; data entered into the Case Report Form (CRF) and electronic database, key data double-entered, randomly reviewed by a third person.
- Reporting: Report serious adverse events (e.g., seizures) to the Yancheng First People's Hospital Ethics Committee, etc., within 24 hours; mild and moderate adverse events summarized and reported weekly in meetings.

**7.3 Patient Withdrawal Handling**

Perform unblinding for withdrawn patients; make every effort to collect the patient's last medical assessment data and basic information; inform the patient that necessary medical consultation and support are still available after withdrawal.

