**5. Evaluation Indicators**

Assessments are conducted at the following time points: pre-intervention (T0), post-intervention at 2 weeks (T1), 4 weeks (T2), and 6-week follow-up (T3). The assessors are not involved in the research process. These assessors have over 5 years of clinical experience and are proficient in the application of assessment tools and methods. Assessors are blinded to group assignment.

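### Section 7.3 unblinds every withdrawn patient, whatever the reason, and does not shield outcome assessors, so blinded scoring of that patient's last FMA-LE is left unprotected.

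*Protocol*

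**What the plan says.** Section 7.3 of the protocol is a single sentence. It begins "Perform unblinding for withdrawn patients; make every effort to collect" the patient's last assessment data, and ends by asking that the patient be told medical support remains available. The unblinding instruction covers all withdrawals. It gives no reason, condition, authoriser, recipient, timing or record. No other section limits it: section 7.2, on adverse events including seizures, does not mention breaking the code.

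The blinding is set out in two other places. Section 3 releases the allocation only to the physical therapist who delivers the intervention, and says that participants and outcome assessors are thereby kept blind. Section 5 adds: "Assessors are blinded to group assignment".

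Section 5.1 makes FMA-LE the primary outcome, with items scored 0, 1 or 2. Section 7.1.1 places it at T0, T1, T2 and the 6-week follow-up (T3). Section 2 allows for dropout by "considering a 20% follow-up loss rate" and concludes that "at least 20 patients are needed per group, totaling 60 patients".

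**The concern.** A reveal is normally reserved for the case where a patient's care depends on knowing the arm. Here it follows from withdrawal itself, so a patient who leaves because of travel is unblinded in the same way as one who has had a seizure.

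The delivering therapist already knows the arm. The instruction therefore has an effect only if the allocation goes to someone from whom section 3 withholds it: the patient, other staff or an assessor. The same sentence asks staff to obtain last assessment data and puts no barrier between the two actions.

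FMA-LE depends on the rater's judgement and the patient's effort, and the sham arm is there to protect both. Withdrawal may also be related to arm, through intolerance or lack of perceived benefit. Any bias would then fall on patients whose outcomes carry information about the treatment comparison. A broken blind cannot be repaired later, and a statistical analysis plan could not restore it.

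**Working it through.** **Inputs**
- Section 2: difference of 3 FMA-LE points, SD 2.5, α = 0.05 (sidedness not stated, two-sided assumed), power 90%, loss 20%, 20 per group, 60 in total.
- Section 3: allocation 1:1:1.
- Assumed here: withdrawal rates of 5% and 10%, because the protocol gives no withdrawal rate as such.

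**Step 1. Reproduce the plan's own figure.** For a two-sample t-test with 16 per group, the noncentrality is (3/2.5) × √(16/2) = 1.2 × 2.828 = 3.39 on 30 degrees of freedom. This gives power 0.907, and 16 is the smallest group size that reaches 0.90. Inflating for loss, 16/(1 − 0.20) = 20 per group and 3 × 20 = 60. The stated size reproduces. The 4 patients per group between 16 and 20 are the loss allowance.

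**Step 2. Count the patients exposed to the rule.** Number unblinded = withdrawal rate × N.

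| Withdrawal rate | Of 60 | Per arm of 20, if evenly spread |
|---|---|---|
| 5% (assumed) | 3 | 1 |
| 10% (assumed) | 6 | 2 |
| 20% (all of the plan's loss allowance) | 12 | 4 |

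The last row is the ceiling under the plan's own allowance. Loss to follow-up includes patients who drop out of contact without withdrawing.

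**Step 3. Set the sections side by side.**

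| Question | Sections 3 and 5 | Section 7.3 |
|---|---|---|
| Who may know the arm? | Only the treating therapist | Not stated |
| Who stays blind? | Participants and outcome assessors | No one is named as protected |
| When may the code be broken? | No provision | At every withdrawal |
| Is assessment kept apart from the reveal? | Assessors blinded, without exception | Both are asked for in one sentence, with no order or separation |

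A site could follow section 7.3 to the letter, tell the patient or an assessor the arm, and then have FMA-LE scored. That would breach sections 3 and 5, and nothing in section 7.3 prevents it.

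**The case against.** The strongest reply is that section 7.3 does not say an assessor learns anything. If the code went only to a treating physician, section 5 could still be honoured. That is right. The documents show an unguarded rule in conflict with the blinding provisions, and they do not show that assessor blinding will in fact be broken.

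Four stronger readings are tempting, and the text does not support them.

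- **That the last FMA-LE will be taken unblinded.** The actions are separated by semicolons and no order is set. The last assessment data may also be data already recorded under the blind. The supportable word is *may*.
- **That later visits are given up, or blinded follow-up is closed off.** Section 7.3 neither schedules nor forbids later visits for withdrawn patients.
- **That 12 patients lose their outcomes because of the rule.** Unblinding removes no data, and the same sentence asks for every effort to collect it. The sample size already treats 4 per arm as not evaluable, so planned power is unchanged. A patient who withdraws after T2 already has a blinded T2, and the analysis in section 6 uses only T0 to T2.
- **That each reveal teaches staff the allocation pattern or the look of the sham.** Section 3 describes a computer-generated sequence in a central web-based system and states no block size. The therapist already knows which patients receive sham. This remains speculation.

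What is left does not depend on any of these. The rule is unconditional, it is not limited elsewhere, and it conflicts with sections 3 and 5. It is an operating instruction for site staff in the protocol itself, so it is more than a detail left to a later document.

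**Conclusion.** The point holds in this form: automatic unblinding at withdrawal conflicts with the blinding that the protocol promises, and it leaves blinded assessment of withdrawing patients unprotected. Its reach is 12 of 60 patients at most under the plan's allowance, and 3 or 6 at assumed withdrawal rates of 5% or 10%. The 12 assumes that all follow-up loss is formal withdrawal. The figure of 4 per arm also assumes an even spread.

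The size of any bias in FMA-LE cannot be derived from the protocol. It depends on who receives the code and on whether an assessment follows the reveal, and neither is stated. A reader might infer that outcome data are lost or that the sample size is invalid; neither follows. The point is still worth correcting before withdrawals occur, because unblinding is irreversible and the correction is cheap.

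**What to change.** Reconcile section 7.3 with sections 3 and 5 by replacing the automatic unblinding with wording to this effect:

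- Allocation stays masked when a patient withdraws.
- The code is broken for an individual only when knowledge of the allocation is needed for that patient's care. Each break is logged and is not disclosed to outcome assessors.
- Any final FMA-LE is done by a blinded assessor before, or separately from, any reveal.
- Patients who stop the intervention but still consent to follow-up are invited to the remaining scheduled assessments. Those who withdraw consent to follow-up are not.

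The cost is a one-paragraph amendment and a few visits that are already in the schedule. The sample size does not change.
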